## Abstract

**Background:**

Hand osteoarthritis is a common and disabling problem without effective therapies. Accumulating evidence suggests the role of local inflammation in causing pain and structural progression in hand osteoarthritis, and hand osteoarthritis with synovitis is a commonly encountered clinical phenotype. Methotrexate is a well-established, low-cost, and effective treatment for inflammatory arthritis with a well-described safety profile. The aim of this multicentre, randomised, double-blind, placebo-controlled trial is to determine whether methotrexate reduces pain over 6 months in patients with hand osteoarthritis and synovitis.

**Methods:**

Ninety-six participants with hand osteoarthritis and synovitis will be recruited through the Osteoarthritis Clinical Trial Network (Melbourne, Hobart, Adelaide, and Perth), and randomly allocated in a 1:1 ratio to receive either methotrexate 20 mg or identical placebo once weekly for 6 months. The primary outcome is pain reduction (assessed by 100 mm visual analogue scale) at 6 months. The secondary outcomes include changes in physical function and quality of life assessed using Functional Index for Hand Osteoarthritis, Australian Canadian Osteoarthritis Hand Index, Health Assessment Questionnaire, Michigan Hand Outcomes Questionnaire, Short-Form-36, tender and swollen joint count, and grip strength, and structural progression assessed using progression of synovitis and bone marrow lesions from magnetic resonance imaging and radiographic progression at 6 months. Adverse events will be recorded. The primary analysis will be by intention to treat, including all participants in their randomised groups.

**Discussion:**

This study will provide high-quality evidence to address whether methotrexate has an effect on reducing pain over 6 months in patients with hand osteoarthritis and synovitis, with major clinical and public health importance. While a positive trial will inform international clinical practice guidelines for the management of hand osteoarthritis, a negative trial would be highly topical and change current trends in clinical practice.

**Trial registration:**

Australian New Zealand Clinical Trials Registry (ANZCTR), ACTRN12617000877381. Registered 15 June 2017, https://www.anzctr.org.au/Trial/Registration/TrialReview.aspx?id=373124

## Background

Osteoarthritis (OA) is the most common chronic joint disease and frequently involves the hand [1]. Hand OA is a common and disabling problem worldwide, resulting in significant disease burden and impaired quality of life. Most middle-aged people have radiographic OA affecting at least one hand joint, with 20% having disabling pain [2]. The age-standardised prevalence of hand OA was 44.2% for females and 37.7% for males in the general population [3], much higher than the prevalence of rheumatoid arthritis (~1%). Hand OA is as disabling as rheumatoid arthritis, impeding activities of daily living such as dressing and eating [4], and has similar clinical importance with regard to health-related quality of life as rheumatoid arthritis [5]. Since the prevalence of hand OA increases with age, the ageing population is expected to drive increasing disease burden and healthcare costs for treating this condition [6]. Despite the high prevalence and disease burden, there is a lack of effective therapies for hand OA. Clinical guidelines for the management of hand OA, such as those from the European League Against Rheumatism suggest topical therapy (preferred over systemic treatments, topical non-steroidal anti-inflammatory drugs (NSAIDs) being first-line choice), oral analgesics (e.g. paracetamol and NSAIDs), and non-pharmacological therapy (education, assistive devices, exercises and orthoses) [7]. However, these therapies only have limited efficacy in reducing pain.

Accumulating evidence suggests that hand OA is a heterogeneous disease involving all joint structures, in which local inflammation plays a central role in causing pain and structural progression [8]. A common phenotype of hand OA is the inflammatory phenotype, characterised by joint swelling (synovitis) [9, 10], and this phenotype represents an aggressive form of disease [11–14]. Imaging studies have shown a high prevalence (approximately 50%) of synovitis in symptomatic hand OA [15, 16], with painful joints significantly more likely to have synovitis than non-painful joints [15, 17, 18]. Synovitis is the strongest predictor for radiographic progression of hand OA over 2 years [11, 12] and 5 years [13, 14], supporting inflammation is a risk factor for rapid disease progression. Therefore, inflammation is a potential treatment target in hand OA, and therapies targeting synovitis may offer a novel approach for reducing disease burden from hand OA.

Recent efforts to examine the effect of anti-inflammatory therapies in hand OA have been limited by including all patients with hand OA, not just those with the synovitis phenotype. A randomised controlled trial showed adalimumab (a tumour necrosis factor blocker) was not superior to placebo to alleviate pain in patients with hand OA not responding to analgesics and NSAIDs [19]. This study was limited by the short duration (6 weeks) and no specific phenotype (i.e. with synovitis) of hand OA being examined. There is proof of concept that targeting synovitis will be effective. In a 1-year randomised controlled trial of patients with symptomatic erosive inflammatory hand OA, etanercept (a tumour necrosis factor blocker) resulted in greater pain reduction, more radiographic remodeling, and less bone marrow lesions compared to placebo in those with inflammation [20]. In another 12-month randomised controlled trial of people with erosive hand OA, adalimumab significantly halted the progression of joint damage in those with synovitis [21]. Based on the histology of the synovium in hand OA [22], there is no biological rationale why specific therapies targeting one inflammatory pathway, such as tumour necrosis factor antagonists, provide effective treatments for hand OA with synovitis. Less specific therapies may offer greater disease modification, since multiple pre-inflammatory cytokines are targeted. Methotrexate is a well-established, low-cost, and effective treatment for inflammatory arthritis with a well-described safety profile. In a Cochrane review of 7 randomised controlled trials comparing methotrexate with placebo in rheumatoid arthritis, methotrexate monotherapy showed a clinically important and statistically significant improvement in symptoms at 52 weeks and significant reduction in radiographic progression [23]. Methotrexate reduced pain in a randomised controlled trial over 6 months and an open-label trial over 24 weeks of knee OA [24, 25]. However, a recently published randomised controlled trial showed no superiority of 10 mg methotrexate weekly over placebo in pain relief at 3 or 12 months in patients with symptomatic erosive hand OA refractory to usual treatments [26]. This study may be limited by the very low dose of methotrexate (10 mg weekly) and not inflammatory phenotype of hand OA being examined. Based on the available data, it is clinically important to determine whether targeting those with hand OA and synovitis is likely to improve the effectiveness of methotrexate on reducing pain and/or slowing structural progression of hand OA.

## Hypothesis and objectives

We propose a randomised, double-blind, placebo-controlled trial to determine the effect of 20 mg methotrexate weekly, compared to placebo, on reducing clinical symptoms and structural progression in people with hand OA and synovitis over 6 months. It was hypothesised that methotrexate will (1) reduce pain (primary hypothesis), and (2) improve physical function and quality of life (secondary hypothesis), and reduce structural progression (secondary hypothesis) over 6 months compared to placebo in people with symptomatic hand OA and synovitis. If methotrexate is proven to be effective, it will offer a novel therapeutic approach to reducing pain and disease progression of hand OA.

## Study design

The METHODS (A randomised controlled trial of METhotrexate to treat Hand Osteoarthritis with Synovitis) study is a multicentre, randomised, double-blind, placebo-controlled trial over 6 months.

## Trial registration

The trial was registered at the Australian New Zealand Clinical Trials Registry prior to recruitment commencing (ACTRN12617000877381, registered 15 June 2017; amended 22 July 2021). The trial reporting will be guided by the Consolidated Standards of Reporting Trials (CONSORT) Statement [27]. Due to the COVID-19 pandemic, the trial was temporarily halted in March 2020, when 80 participants had been randomised with 60 participants taking study medication for at least 6 months. Due to potential safety concerns at that time, participants were asked to stop study medication. The trial was resumed in November 2020. The 7 months when participants were off treatment due to safety concerns regarding the possibility of COVID infection in those taking methotrexate, would interfere with the validity of the use of the primary outcomes assessed at 2 years for hand pain and radiographic progression. However, the use of pain measured at 6 months will provide a valid measure to test whether methotrexate improves pain. In November 2020, the protocol was amended to make pain reduction at 6 months as the primary outcome, and radiographic progression at 6 months as a secondary outcome. Accordingly, the other secondary outcomes were also amended, which included changes in physical function, quality of life, joint activity, and grip strength at 6 months, and progression of synovitis and bone marrow lesion at 6 months after the amendment. The amendment was submitted to the Australian New Zealand Clinical Trials Registry in November 2020 and updated in July 2021.

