### Sample size calculation

The average VAS pain in a previous clinical trial of symptomatic hand OA similar to the proposed study was 54 mm (standard deviation 20 mm) [43]. The minimal clinically important difference to be detected in OA trials is a 15 mm change in VAS pain (out of 100 mm) [44]. We will require 38 participants in each group to attain a power of 90% to detect the minimal clinically important difference (alpha 0.05, two-sided significance). Accounting for an estimated 20% loss to follow-up, we will recruit 96 participants, 48 in each group.

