### Statistical analyses

Analyses will be conducted in Stata v16 or later. An intention-to-treat analysis, including all participants in their randomised groups regardless of their adherence to assigned treatments, will be performed in a blinded fashion. The effect of intervention on pain reduction and other pain and function outcomes measured at multiple time points (for pain: week 4, month 3 and month 6; for secondary pain and function measures, month 3 and month 6) will be analysed using mixed linear regression models, with a random intercept for participant. Models will be adjusted for the baseline measure and the stratifying variables of site and gender, and include categorical terms for time, a term for randomised group and terms for the interaction between randomised group and time. Results will be presented as mean differences between groups at each time point with 95% confidence intervals, and p-values will also be reported. For measures only taken at baseline and a single follow-up time point, regression models will omit random intercepts and terms for time. Regression modelling assumptions will be assessed graphically. In the case of a gross departure from normality of residuals, ranked based techniques will be applied. As stipulated by OARSI clinical trial recommendations [28], binary logistic regression will be used to assess the effect of intervention on structural progression at 6 months, adjusted for the stratifying variables of site and gender. The outcome of tender/swollen joint count will be analysed via a Poisson model fit via generalised estimating equations with an exchangeable working correlation structure to account for multiple measurements per participant. This model will include the baseline measure and the stratifying variables of site and gender, and include categorical terms for time, a term for randomised group and terms for the interaction between randomised group and time. If more than 5% of participants are missing their primary outcome, multiple imputation will be applied to account for missing data, with missing values imputed separately by treatment group. Sensitivity analyses will fit outcome regression models additionally adjusted for age, body mass index, and severity of radiographic OA and synovitis if baseline imbalances between randomised groups with respect to these variables are considered clinically important. A sensitivity analysis of the primary outcome will be undertaken to estimate the effect of methotrexate under the assumption of hypothetical complete compliance to treatment by applying a two-stage least squares instrumental variables approach [45], where full compliance will be defined as participants taking at least 80% of their medication.

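### Month-6 pain is called valid and 90% power is kept, yet up to 20 of the 80 participants randomised before the COVID-19 halt were stopped inside the new 6-month window, which dilutes the intention-to-treat effect

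*Protocol article*

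**What the plan says.** All references are to the Protocol article.

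- **Trial registration (section after Study design).** The trial was halted in March 2020, "when 80 participants had been randomised with 60 participants taking study medication for at least 6 months". At that point "participants were asked to stop study medication". It resumed in November 2020. "The 7 months when participants were off treatment due to safety concerns" are given as the reason why the 2-year outcomes are no longer usable. The primary outcome was therefore moved to 6 months, on the ground that "the use of pain measured at 6 months will provide a valid measure to test whether methotrexate improves pain".
- **Sample size calculation.** With a 15 mm difference, an SD of 20 mm and two-sided alpha of 0.05, 38 per group are required for 90% power. "Accounting for an estimated 20% loss to follow-up, we will recruit 96 participants, 48 in each group". The halt is not mentioned.
- **Statistical analyses.** The primary analysis is by intention to treat, "including all participants in their randomised groups regardless of their adherence to assigned treatments". Multiple imputation applies if more than 5% of primary outcomes are missing. A two-stage least squares (2SLS) sensitivity analysis estimates the effect under complete compliance, defined as taking at least 80% of medication. None of this refers to the halt.

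**The concern.** The argument for moving the endpoint is that time off treatment spoils the 2-year comparison but leaves the 6-month one intact. That holds for the 60 who had already had 6 months on drug and for anyone randomised after the restart. It does not hold for participants who were part-way through their first 6 months in March 2020. The section's own counts show that there may be as many as 20 of them, and nothing in the article addresses them.

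The stop was ordered by the trial in both arms. It is neither ordinary non-adherence nor part of the strategy in the Hypothesis and objectives section, which is weekly methotrexate against placebo over 6 months. Pooling scores taken after the stop mixes the effect of 6 months of treatment with the effect of a shorter course followed by withdrawal. If the drug works, the mixture shrinks the difference. The Discussion says a negative trial would change clinical practice, so a bias towards the null matters here.

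**Working it through.** **Inputs from the article:** 80 randomised and 60 with at least 6 months on drug at the halt; target 96; difference 15 mm; SD 20 mm; two-sided alpha 0.05; 20% loss; 1:1 allocation.

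**Assumptions:** the share of the effect retained by interrupted participants; an even split of them across arms; recruitment ending at 96; SD unchanged at 20 mm.

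**1. The plan's own figure.** n per arm = 2 × (1.960 + 1.282)² × (20/15)² = 37.4, so 38. Then 38/0.8 = 47.5, so 48 per arm and 96 in total. Both figures reproduce. Power at 38 per arm is 90.5% by the normal approximation and 89.7% by the t-test. The t-test is used below.

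**2. How many, and when.** 80 − 60 = 20, which is 25% of those randomised by then and 20.8% of 96. Anyone with under 6 months on study in March 2020 reached nominal month 6 by about September 2020, before the November restart. An on-schedule score from an interrupted participant is therefore off drug. The article does not say whether any of these visits were deferred.

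**3. The 20 counted as lost.** 96 − 80 = 16 remain to be recruited.
- No other loss: 60 + 16 = 76, or 38 per arm. Power is 89.7%.
- 20% loss among the 16 as well: 60 + 12.8 = 72.8, or 36.4 per arm. Power is 88.4%.

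**4. The 20 kept, as intention to treat implies when their scores are observed.** Mean effect = 15 × [1 − s × (1 − r)], where s is the interrupted share of those analysed and r is the share of effect they retain.

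| r | 46.4 per arm, s = 20/92.8 | 38.4 per arm, s = 20/96 |
|---|---|---|
| 0 | 11.8 mm, 80% | 11.9 mm, 73% |
| 25% | 12.6 mm, 85% | 12.7 mm, 78% |
| 50% | 13.4 mm, 89% | 13.4 mm, 83% |
| 75% | 14.2 mm, 92% | 14.2 mm, 87% |

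The first column loses 20% of the 16 later recruits only: (60 + 12.8 + 20)/2 = 46.4. The second loses 20% of everyone: 96 × 0.8/2 = 38.4.

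Worst case: all 20 are among 76 analysed and retain no effect. The mean effect is 15 × (1 − 20/76) = 11.1 mm, and power at 38 per arm is 66%.

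**5. If fewer were interrupted.** With s = k/96, no retained effect and 38 per arm, power is 86% for k = 5, 82% for k = 10, 78% for k = 15 and 72% for k = 20.

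**6. Baseline adjustment.** The model adjusts for baseline pain, but the sample size does not use this. If the baseline-outcome correlation is 0.3 or 0.5 (assumed), the 72% for k = 20 in step 5 rises to 76% or 84%.

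**The case against.** The strongest reply has four parts.

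**The comparison remains valid.** Both arms were told to stop, so randomisation protects the test and type I error is not inflated. Intention to treat regardless of adherence is a legitimate treatment-policy question. This stands. A reader might infer that month-6 pain is invalid as an outcome, and the article does not support that. What changes is the quantity estimated.

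**The loss allowance may absorb the problem.** This largely stands if the 20 are treated as lost, as step 3 shows. A reader might go further, take 20% off all 76 undisturbed participants (76 × 0.8/2 = 30.4 per arm, power 82%) and conclude that no room is left for ordinary loss. That is not supported. Sixty of the 76 had already had 6 months on drug, so there is no reason to charge them a fresh 20%, and ordinary loss among the first 80 may already sit within the 20.

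**Twenty is a ceiling.** This stands. If 20% of the first 80 had already stopped (16, as an illustration), only 4 would have been interrupted. The article gives no split.

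**Existing analyses, or a separate analysis plan, may cover it.** This stands only in part. Week-4 and month-3 scores enter the mixed model, but multiple imputation acts on missing scores, and an off-drug score is observed. The 2SLS analysis is aimed at dilution, but it is a sensitivity analysis, splits compliance at 80%, and does not say whether drug withheld by the trial counts against a participant. Visit-handling detail may well sit in a plan that is not shown. The unqualified validity sentence and the unrevised power statement are in this article.

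**Conclusion.** The concern holds in a limited form. The article's justification for its amended primary endpoint is stated too broadly: it ignores up to 20 participants whose 6-month treatment window the halt may have cut short. Pooling their off-drug scores dilutes the estimated effect of 6 months of methotrexate. If all 20 were interrupted and retained no effect, the expected 15 mm becomes about 11 to 12 mm; if they retained 75%, it becomes about 14 mm.

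A reader might conclude that the 90% power is false. The documents do not show that. It is a figure that depends on handling the article does not state: close to 90% if these participants count as the loss allowance, and between 66% and 92% if they are kept. These values rest on 20 as an upper bound, assumed retained effects and an unadjusted t-test. Baseline adjustment would recover part of any shortfall.

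**What to change.** 1. In Trial registration, state how many participants were interrupted by the halt within 6 months of randomisation, separately from those who had already stopped. Define their month-6 assessment by time from randomisation.
2. In Statistical analyses, prespecify before unblinding an analysis of the primary outcome that sets pain scores recorded after the trial-wide instructed stop to missing and keeps only those from before it. Some month-3 scores will drop out as well. Missing-at-random is plausible, because the stop applied to everyone and did not depend on arm or pain. Report this beside the all-data intention-to-treat estimate.
3. State whether drug withheld by the trial counts against the 80% compliance definition in the 2SLS analysis.
4. Qualify the validity sentence so that it covers participants with an uninterrupted window and says what the intention-to-treat estimate means for the others. In Sample size calculation, restate power under the chosen handling, with its assumptions.

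The cost is some wording, one extra model run and a less favourable stated power. No new participants or data are needed. The choices in items 1 to 3 should be made while the statisticians are still blinded, because they lose credibility once allocation is known.

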## Ethics approval

Ethics approval has been obtained from Alfred Hospital Ethics Committee (290/17), Monash University Human Research Ethics Committee (10725), University of Tasmania Human Research Ethics Committee (H0016794), Central Adelaide Local Health Network Human Research Ethics Committee (HREC/18/CALHN/458), and South Metropolitan Health Service Human Research Ethics Committee (RGS0000000573). Written informed consent will be obtained from all the participants.

## Methods

### Study setting and participants

Eligible participants with hand OA and synovitis will be recruited through the Osteoarthritis Clinical Trial Network (Melbourne, Hobart, Adelaide, and Perth, Australia), from the community via advertisements and from medical practitioners.

#### Inclusion criteria

(1) aged 40-75 years; (2) a pain score of at least 40 on a 100 mm visual analogue scale (VAS) and radiological OA (Kellgren and Lawrence grade >2) in >1 joint, as recommended by the Osteoarthritis Research Society International (OARSI) clinical trials guidelines for hand OA [28]; (3) evidence of synovitis determined from magnetic resonance imaging (MRI) according to the Outcome Measures in Rheumatology (OMERACT) hand OA recommendations and with a grade ≥1 in ≥1 joint [29].

#### Exclusion criteria

(1) concomitant rheumatic disease, inflammatory joint disease, psoriatic arthritis, ankylosing spondylitis, or gout; (2) contraindication to methotrexate [e.g. renal, liver or haematological condition, cancer including skin cancer, serious infections requiring hospitalisation in the last 5 years, known or past infection with human immunodeficiency virus, hepatitis B or C, tuberculosis, or known lung disease with scarring (any fibrosis or evidence of past tuberculosis exposure on chest x-ray), concurrent regular prednisolone use, taking regular trimethoprim or bactrim antibiotics, egg or flu vaccination allergy]; (3) contraindication to MRI (e.g. implanted pacemaker, metal sutures, presence of shrapnel or iron filings in the eye, or claustrophobia); (4) unable to complete informed consent; (5) women who are pregnant, breast-feeding or trying to become pregnant, or men who father a child.

